#### Compliance

The randomised intervention in this trial is the dressing (standard or NPWT) applied to the closed fracture wound at the end of surgery. This intervention occurs at a single time point, and compliance is therefore defined as the proportion of participants in each arm receiving the treatment to which they were randomised. The number (and percentage) of participants receiving the assigned dressing and receiving another dressing or no dressing in each arm will be summarised as well as the reasons for not receiving the randomised treatment. Details of what was provided instead will also be summarised.

#### Analysis of primary outcome

The numbers and percentages of ‘deep infections’ occurring up to 30 days post-randomisation in the two study intervention groups, NPWT and standard dressing, will be calculated. The rates of deep infection in the two study groups will be compared using a mixed effects logistic regression model. The model will include a random effect to account for any heterogeneity in the response due to recruitment centre. Fixed effects to adjust for open versus closed fractures, ISS level (≤ 15 vs ≥ 16), participant age, and participant gender will also be included. Participant age and gender are included in the model since there is evidence that older men have worse outcomes after major trauma. The result will be reported as an odds ratio (OR) with associated 95% confidence interval and *p* value for comparison between the two treatment groups. The unadjusted OR and associated 95% confidence interval will also be reported.

This analysis will be conducted for the ITT population using the available case dataset. As sensitivity analyses, the analysis will be repeated for: (i) the ITT population using an imputed dataset (best case worst case analysis); and (ii) the PP population using the available case dataset. In addition, a sensitivity analysis taking account of the competing risk of death [26] will be conducted if a sufficient number of deaths have occurred prior to 30 days, that is if more than 5% of participants have died prior to this time point.

If a significant treatment effect of NPWT is identified in the primary analysis, an exploratory subgroup analysis will be conducted to investigate whether this effect is moderated by the underlying risk level of the wound. This will be done by repeating the primary analysis and including wound location (above or below the knee) as a covariate. Wound location will be used as a proxy for wound risk level due to differences in soft-tissue cover; there being less soft-tissue cover below the knee.

The main analysis of the primary outcome (ITT population using the available case dataset) will be repeated using the alternative definition of ‘deep infection’, including infections occurring up to 90 days after injury. If any of the sensitivity analyses conducted for the primary endpoint (30 days) demonstrated substantially different results from the primary analysis, these analyses will be repeated for the rates of deep infection up to 90 days.

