## Methods and design

### Trial design

WHIST is a multicentre, two-arm, parallel-group, superiority randomised controlled trial designed to compare the rates of ‘deep infection’ in patients allocated to standard wound dressing versus those allocated to NPWT. Eligible patients are randomised on a 1:1 basis using minimisation to balance the two treatment groups by trial centre, open or closed fracture at presentation, and Injury Severity Score (ISS) ≤ 15 versus ISS ≥ 16. Neither participants nor their treating surgeons are blind to treatment allocation since wound dressings are clearly visible. The primary outcome is assessed at 30 days after randomisation with secondary outcomes assessed at baseline, 30 days, and 3 and 6 months after randomisation. Full details of the trial design, study population, and study procedures have been published previously [14].

The trial is registered with the International Standard Randomised Controlled Trials database, ISRCTN reference number ISRCTN12702354.

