### Sample size

Only one previous randomised trial has compared NPWT to standard dressings for surgical incisions associated with major trauma to the lower limb [12]. This trial indicated that the rate of ‘late’ (deep) infection was reduced by 6%; from 15% in the standard treatment group to 9% in the NPWT group.

In the absence of a minimum clinically important difference for deep wound infection, we surveyed surgeons in the UK Orthopaedic Trauma Society who perform surgery for major trauma to the limbs (unpublished data, 2015). This survey showed that a 6% reduction in the rate of ‘deep infection’ would, universally, be sufficient to change clinical practice with regard to the choice of dressing. Therefore, assuming a reduction in the proportion of patients having a deep infection from 15% to 9%, 615 patients would be required in each group to provide 90% power at the 5% level (two-sided) when comparing two independent proportions. Previous experience in clinical trials of lower limb fracture surgery for major trauma indicates that up to 20% of the primary outcome data may be lost during the follow-up period due to death and loss to follow-up [23]; therefore, we propose to recruit 1540 patients in total for this trial (770 per arm).

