**Fig. 1 Fig1:**
[figure not shown]
CONSORT flow diagram for participants in trial up to 6 months follow-up

The baseline comparability of the two randomised groups in terms of (i) minimisation factors, (ii) baseline characteristics (Table 1), (iii) operative procedure details (Table 2), and (iv) secondary outcomes at baseline will be presented. Numbers with percentages will be used to compare binary and categorical variables, and either means and standard deviations or medians and interquartile ranges will be used for continuous variables. There will be no tests of statistical significance nor confidence intervals for differences between the randomised groups.

**Table 1 Tab1:** Baseline characteristics

Baseline characteristic	Type	Levels or scale
Sex	Binary	Male; female
Age	Continuous	Years
BMI	Continuous	kg/m^2^
Marital status	Categorical	Single; separated; married/civil partner; living with a partner; divorced; widowed
Ethnicity	Categorical	White; Black Caribbean; Black African; Black other; Indian; Pakistani; Bangladeshi; Chinese; other
Training post school	Categorical	None; formal work qualification; college/university non-degree; degree from college/university
Employment status	Categorical	Full-time employed; part-time employed; self-employed; retired/looking after home/inactive; unpaid work; unemployed; full-time student
Mechanism of injury	Categorical	Low energy fall; high energy fall; road traffic accident; crush injury; contact sports injury; other
Any other injuries	Binary	Yes; no
Diagnosed with diabetes	Binary	Yes; no
Regular smoker	Binary	Yes; no
Alcohol consumption per week	Categorical	0–7 units; 8–14 units; 15–21 units; more than 21 units
Regular analgesia before injury	Binary	Yes; no
Other medication before injury	Binary	Yes; no

**Table 2 Tab2:** Operative procedure details

Operative procedure detail	Type	Level or scale
Lead surgeon grade	Categorical	Consultant; associate specialist; specialist trainee; other
Number of surgeons	Continuous	NA
Wound limb	Binary	Right; left
Wound location	Categorical	Hip; femur; patella; tibia; foot
How fixed	Categorical	Nail; plate and screws; wire/tension band wires; half-pin; fine pin; other
How closed	Categorical	Interrupted sutures; skin clips; subcuticular suture; any skin closure used; steristrips; glue; other
Intra-operative complications	Binary	Yes; no
If yes what	Categorical	Nerve injury; vascular injury; tendon injury; extension of fracture; other
Any other surgery	Binary	Yes; no

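### The wound-location subgroup analysis aims to test moderation of the NPWT effect, but the model given for it has no treatment-by-location term and cannot do so

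*SAP article*

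**What the plan says.** The Analysis of primary outcome section compares deep infection between arms with a mixed effects logistic model. It has a random effect for centre and fixed effects for open or closed fracture, ISS level, age and gender, and the result is one OR for treatment.

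The same section then adds a conditional step: "If a significant treatment effect of NPWT is identified in the primary analysis, an exploratory subgroup analysis will be conducted". The stated purpose is to see whether the treatment effect is moderated by the underlying risk of the wound. Location relative to the knee stands in for risk because there is less soft tissue below the knee. The method follows in one sentence: "This will be done by repeating the primary analysis and including wound location (above or below the knee) as a covariate". Neither a treatment-by-location interaction nor a separate OR for each location is mentioned.

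In Analysis of secondary outcomes, by contrast, interactions between treatment and time are named outright, both for the continuous outcomes and for the DN4.

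**The concern.** Moderation means that the treatment effect differs between locations. A location main effect lets the baseline risk differ by location, but holds the treatment OR equal in the two. The stated method therefore does not address the stated aim, whatever the data show.

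An analyst who follows the text would obtain a location-adjusted version of the primary OR. If it came out close to the primary OR, as it often would, it could be reported as evidence that wound risk does not alter the effect, although that was never tested. An analyst who noticed the problem would have to choose another model after seeing the primary result, which is what a published analysis plan is meant to prevent. This is the only subgroup question in the article, and it bears on which wounds might benefit.

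**Working it through.** **1. The plan's own figure.** Inputs from the Sample size section: 15% versus 9%, two-sided 5% level, 90% power. With pooled variance and no continuity correction:

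n = [1.960 × √(2 × 0.12 × 0.88) + 1.2816 × √(0.15 × 0.85 + 0.09 × 0.91)]² / 0.06² = 614.4, so 615 per group, as stated.

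Dividing by 0.8 for 20% loss gives 769, rounded in the plan to 770. The design OR is (0.09/0.91) / (0.15/0.85) = 0.56.

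**2. The two models.** Let T = 1 for NPWT and L = 1 for below the knee. The other covariates and the centre effect are the same in both models and are left out here.

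- As written: logit(p) = a + bT + cL. The treatment OR is exp(b) above the knee and exp(b) below it. Their ratio is 1 by construction.
- With interaction: logit(p) = a + bT + cL + dTL. The treatment OR is exp(b) above and exp(b + d) below. The ratio of odds ratios (ROR) is exp(d), which is the moderation parameter.

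This step needs no assumed figures.

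**3. What the model as written returns under moderation.** The document gives neither the share of wounds below the knee nor infection rates by location, so the following are assumptions: 615 analysed per arm, 60% of wounds below the knee, 19% versus 9% below, 9% in both arms above. The overall standard-dressing rate is 0.6 × 19% + 0.4 × 9% = 15% and the NPWT rate is 9%, which matches the design. Both models were fitted to expected cell counts, without centre and the other covariates.

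- True OR below: (0.09/0.91) / (0.19/0.81) = 0.42. True OR above: 1.00.
- Model as written: one OR of 0.56 (95% CI 0.39 to 0.80), the same as the overall OR of 0.56.
- Interaction model: ROR 0.42, standard error of log ROR 0.387. Power is Φ(|ln 0.42| / 0.387 − 1.96), about 61%.

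**4. Can it tell moderation from none?** Two further assumed data sets, 615 per arm, half of the wounds below the knee, standard-dressing rates 10% above and 20% below:

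| | True OR above | True OR below | OR, model as written (95% CI) | ROR, interaction model (95% CI) |
|---|---|---|---|---|
| A: effect only below (10% v 10%; 20% v 8%) | 1.00 | 0.35 | 0.559 (0.39 to 0.80) | 0.35 (0.17 to 0.72), p = 0.004 |
| B: same OR in both | 0.56 | 0.56 | 0.561 (0.39 to 0.80) | 1.00 (0.47 to 2.11) |

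The model as written gives practically the same answer in A and B. The interaction model separates them.

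**5. What the corrected analysis could detect.** Take 615 per arm, rates of 15% and 9%, and s the share below the knee:

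Var(log ROR) = Σ over the two locations of [1/(n × 0.15 × 0.85) + 1/(n × 0.09 × 0.91)], with n = 615s and 615(1 − s).

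| s | SE of log ROR | Power for ROR 0.56 | ROR detectable with 80% power |
|---|---|---|---|
| 30% or 70% | 0.39 | 31% | 0.33 |
| 50% | 0.36 | 36% | 0.36 |

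**The case against.** **Loose drafting.** The text calls this a subgroup analysis and names moderation as its purpose, so a statistician guided by that purpose would probably add the product term anyway. That is plausible, but it shows that the purpose and the method disagree. Because the plan names interactions explicitly elsewhere, the word covariate cannot safely be read as one. Nor is this a detail left to a fuller document: the method is stated, and it does not match its aim.

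**Low stakes.** The analysis is labelled exploratory, and General analysis principles rests the trial's conclusion on the primary analysis alone. This stands, and it limits the severity.

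**Low power.** An interaction test would usually be weak here. This also stands, but it is a reason to put the confidence interval first, not to keep a model that has no moderation parameter.

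**Stronger readings that the document does not support.** A reader might infer that running the analysis only after a significant primary result is itself an error, because offsetting effects could then go unexamined. That cost is real, but the condition also guards against rescuing a null trial through a subgroup. It is a defensible choice for an exploratory analysis. In the scenario of step 3, where the overall rates equal the design rates, the condition would be met about 90% of the time. Nothing in the document suggests harm above the knee, which a scenario of opposite effects needs. A reader might also object that Table 2 records "Hip; femur; patella; tibia; foot" without saying on which side of the knee the patella falls. That is a coding detail which an article may leave to the full plan.

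**Conclusion.** The point holds for the model specification. As written, the analysis yields one OR common to both locations and cannot answer the question set for it. This follows from the form of the model and rests on no assumed rates. The figures only illustrate it. With true ORs of 0.42 and 1.00 the model returns about 0.56, which is also the overall OR. They assume 615 analysed per arm, a 60% below-knee share and the stated location-specific rates, and they omit centre and the other covariates.

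This should be fixed, but it does not put the trial's main result at risk: the primary analysis, its p value and the sample size are unchanged. Neither the significance condition nor the patella category is part of the error.

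**What to change.** Replace the method sentence so that the primary model is refitted with wound location and a treatment-by-location interaction. Report the ratio of odds ratios with its 95% CI and the interaction p value, together with the OR and 95% CI in each location.

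Keep the exploratory label, and say that interpretation rests mainly on the confidence interval, since a non-significant interaction would not show that the effect is the same in both locations.

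The cost is about two sentences and one model term, using data already being collected.

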### Outcomes

#### Primary outcome

The primary outcome for this study is the rate of deep infection; the Centre for Disease Control and Prevention (CDC) definition of a “deep surgical site infection”—a wound infection involving tissues deep to the skin that occurs within 30 days of injury [16]—is used. Since the trial began, the CDC definition of a deep surgical site infection has been modified to include wound infections occurring up to 90 days after injury if metal implants are used in the fracture fixation [17]. Although not all wounds associated with lower limb fracture surgery contain implants, this is the most common method of fixation and therefore we will incorporate this alternative definition of the primary outcome in a supplementary analysis to ensure the study can be utilised in future systematic reviews and meta-analyses.

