#### Loss to follow-up, withdrawals, and missing data

The numbers (and percentages) of losses to follow-up and withdrawals along with reasons for these will be reported by intervention arm at each time point. To ensure that differential losses do not occur between the two groups this will be tested using absolute risk differences (with 95% confidence intervals) and a chi-squared test. Any deaths and their causes will be reported separately.

The patterns of availability of data for primary and key secondary outcomes, from baseline to end of follow-up, will be summarised for the two treatment groups (as number and percentage of individuals missing). Reasons for missing-ness will also be presented, if known. Where appropriate, differentiation will be made between partially completed and fully missing outcome data. Two analysis datasets will be considered: (i) the available case dataset, consisting of all observed data; and (ii) the imputed dataset, where missing data are imputed. Missing data on the primary outcome will be imputed using a best case worst case analysis, considering the situation where all participants in the Standard dressing group with missing data are assumed to have a deep infection and all participants in the NPWT group with missing data are assumed not to have a deep infection and vice versa. Missing data on continuous outcomes will be imputed using multiple imputation (MI) under the missing at random (MAR) assumption. The suitability of the MAR assumption will be considered.

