The DN4 will be analysed using similar methods to those outlined for the primary outcome. The number and proportion of individuals deemed to have neuropathic pain (DN4 ≥ 3) will be reported for each treatment arm. A multi-level mixed-effects logistic regression model with repeated measures (level 1) nested within participants (level 2) will be used. The model will be adjusted for recruitment centre as a random effect (level 3), and fixed effects will be included to adjust for open versus closed fractures, ISS level (≤ 15 vs ≥ 16), participant age, and participant gender. Trends over time will be examined, and, if appropriate, interactions between treatment and time will be included. Results will be presented as ORs with associated confidence intervals. The unadjusted OR and associated 95% confidence interval will also be reported. This analysis will be conducted for the ITT population using the available case dataset.

Similar methods will also be used to analyse complications. The number and percentage of people experiencing each complication in each treatment arm will be reported. If there are sufficient numbers of events, a mixed-effects logistic regression model will be used to compare the rates of complications between intervention arms. The model will include a random effect for recruitment centre and fixed effects for open versus closed fractures, ISS level (≤ 15 vs ≥ 16), participant age, and participant gender. If there are not sufficient numbers of events to fit an adjusted model, unadjusted differences between intervention arms will be calculated using a chi-squared test. This analysis will be conducted for the ITT population using the available case dataset. Temporal patterns of complications will be presented graphically and, if appropriate, a time-to-event analysis (Kaplan-Meier survival analysis) will be used to assess the overall risk and risk within individual classes of complications.

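### The 90-day deep-infection analysis has no scoring rule for participants lost between day 30 and day 90; read literally, it inflates both arms' 90-day rates

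*SAP article*

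**What the plan says.** Under Analysis of primary outcome, the SAP article repeats the main analysis (mixed effects logistic regression, ITT population, available cases) with the outcome widened to deep infection "including infections occurring up to 90 days after injury". Under Loss to follow-up, withdrawals, and missing data, it defines "the available case dataset, consisting of all observed data". No rule is given for a participant last seen infection-free between day 30 and day 90.

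Under Primary outcome, the 90-day version is called supplementary and is added "to ensure the study can be utilised in future systematic reviews and meta-analyses".

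Four other provisions bear on the point:
- The 30-day sensitivity analyses are repeated at 90 days only if one of them gave a substantially different answer at 30 days.
- The competing-risk analysis depends on deaths before day 30.
- Losses are compared between arms at each time point by a risk difference and a chi-squared test.
- For complications, the plan says: "Temporal patterns of complications will be presented graphically and, if appropriate, a time-to-event analysis", and names Kaplan-Meier.

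**The concern.** The 90-day outcome is cumulative. An infection by day 30 is already a 90-day event, whatever follow-up comes later. Absence of infection to day 90 can be observed only in someone followed to day 90. If the analysis takes every participant whose 90-day status is observed, infected participants are retained more fully than uninfected ones, and inclusion depends on the outcome even when loss is completely random.

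The per-arm 90-day percentages are then too high. These are the figures that a systematic reviewer would extract, which is why the plan adds the analysis. If loss, or the timing of infections, differs between the arms, the odds ratio moves as well. The other ways of scoring the same participants give different numbers, so leaving the rule open also leaves a choice to be made once data are in hand.

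**Working it through.** **The plan's own figure.** The Sample size section states "615 patients would be required in each group to provide 90% power at the 5% level (two-sided) when comparing two independent proportions", for 15% v 9%. With pooled variance and no continuity correction:

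n = [1.960·√(2×0.12×0.88) + 1.282·√(0.15×0.85 + 0.09×0.91)]² / 0.06² = 614.4, so 615 per group.

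Then 615/0.80 = 769 per arm, or 1538 in total, against 1540 stated. The plan's figures reproduce.

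**Inputs.**
- From the document: 30-day risks of 15% and 9%; 1548 recruited (Trial status), so 774 per arm; and a ceiling on loss, "up to 20% of the primary outcome data may be lost during the follow-up period due to death and loss to follow-up".
- Assumed, because the document gives neither: a further 3.0 and 1.8 points of infection between day 30 and day 90, making the true 90-day risks 18.0% and 10.8%; and loss of 5%, 10% or 20% after day 30 among those infection-free at day 30, unrelated to later infection. For simplicity nobody is lost earlier.

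**Per-arm rates on the literal reading.** With p the 30-day risk, a the added risk and l the loss:

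reported risk = [p + a(1−l)] / [p + (1−p)(1−l)]

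For standard dressing at l = 0.20 this is (0.15 + 0.024)/(0.15 + 0.68) = 0.174/0.83 = 21.0%.

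| Loss after day 30 | Standard | NPWT | Difference (points) | Odds ratio |
|---|---|---|---|---|
| 0% (truth) | 18.0% | 10.8% | 7.2 | 0.55 |
| 5% | 18.6% | 11.2% | 7.4 | 0.55 |
| 10% | 19.3% | 11.7% | 7.7 | 0.55 |
| 20% | 21.0% | 12.8% | 8.2 | 0.55 |

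The standard-arm error is 0.6 to 3.0 points, against a standard error of √(0.18×0.82/774) = 1.4 points. Participants dropped despite known infection-free status at day 30 number 774×(0.85+0.91)×l, about 68, 136 or 272.

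**Odds ratio.** If f is the share of 90-day infections occurring by day 30 and q the later loss, then reported odds = true odds × [f/(1−q) + (1−f)]. Equal f and q cancel between arms. Otherwise:
- No true effect, 12% + 3% in each arm (f = 0.8), loss 20% standard v 15% NPWT: factors 1.200 and 1.141, odds ratio 0.95. Simulated type I error is 6.3%.
- Same, loss 20% v 10%: factors 1.200 and 1.089, odds ratio 0.91. Simulated type I error is 10.1%.
- Equal loss of 20%, but f = 0.9 on standard and 0.5 on NPWT: 1.125/1.225, so a true odds ratio of 1.00 becomes 0.92.

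**Other scoring rules, same inputs, 20% loss.**
- Lost participants scored as uninfected: 0.15 + 0.024 = 17.4% and 0.09 + 0.0144 = 10.4%, both too low.
- Day-90 follow-up required of everyone: no bias if loss is uninformative. If infected participants are lost at the same rate, however, about 0.20×774×(0.15+0.09) = 37 recorded infections are discarded.

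**Does a censoring-aware estimate repair it?** In a simulation with true risks of 15% and 9%, f = 0.7, and loss of 10% (standard) and 20% (NPWT) spread evenly over days 30 to 90, available cases gave 16.2% v 10.7% (odds ratio 0.620). Kaplan-Meier gave 15.0% v 9.0% (odds ratio 0.560, the true value).

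**The case against.** The strongest reply is that the asymmetric scoring is inferred. The article never says that early infections are kept while infection-free participants lost later are dropped, and a condensed article may leave scoring detail to the protocol. A reader might infer that the plan prescribes this rule; it does not. The literal reading of available cases leads there, but the firm statement is that no rule is given.

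The loss figures can also be challenged. The 20% is a ceiling for primary-outcome data, deaths included, not a rate for days 30 to 90. Because signs of infection are recorded up to 6 months, a missed 3-month contact need not leave day-90 status unknown. Both points stand, and at 5% loss the error is within half a standard error.

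Third, the planned effect measure is the odds ratio, which is protected when loss and timing are equal. A gap of 20% v 10% would be plain in the planned comparison of losses: among about 681 per arm infection-free at day 30, z = 0.10/√[(0.16+0.09)/681] = 5.2. That is right, but the test reveals the imbalance without correcting the estimate, and it does nothing for the per-arm rates.

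The remaining safeguards are weak. Loss after day 30 cannot trigger the 90-day sensitivity repeat, deaths after day 30 cannot trigger the competing-risk analysis, and Kaplan-Meier is conditional and confined to complications.

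**Conclusion.** The point holds with limits. The 90-day analysis lacks a scoring rule for incomplete follow-up, and its literal reading biases the per-arm percentages upward: a true 18.0% becomes 18.6% to 21.0%, and a true 10.8% becomes 11.2% to 12.8%, for 5% to 20% loss. These sizes rest on assumed late infections and assumed uninformative loss after day 30. The documents supply neither figure.

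Two stronger conclusions are not supported. One is that the 90-day odds ratio is biased in any event: it moves only if loss or infection timing differs by arm, and the document gives no evidence that either does. The other is that the trial's main result is compromised: the 90-day analysis is supplementary, and General analysis principles rests the conclusion on the primary analysis of the 30-day outcome. What is at stake is the usefulness of the 90-day figures for evidence synthesis, their stated purpose. The change should be made, but it is not critical.

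**What to change.** 1. Report the per-arm 90-day risks and their difference, with 95% confidence interval, as cumulative incidence at day 90. Use the date of first deep infection, censor at the last date known infection-free (at least the 30-day assessment where that was completed), and treat death as a competing event.
2. Keep the adjusted logistic odds ratio beside it, with a stated rule for incomplete day-90 follow-up. One option is multiple imputation of 90-day status given 30-day status, arm and the model covariates.
3. Run the 90-day missing-data sensitivity analysis regardless of what the 30-day sensitivity analyses show.

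The cost is SAP wording and a modest amount of extra analysis. It needs infection dates and last-contact dates; the time-to-event analysis contemplated for complications already presupposes such dates, but the article does not document that they are recorded reliably, so this should be checked. The estimates assume that loss is uninformative given 30-day status, and the reported 90-day percentages would be somewhat lower than on the literal available-case reading.

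### Sensitivity analyses of the 90-day deep-infection outcome depend on an undefined judgement about 30-day results, so they cannot respond to missing outcomes or deaths between days 31 and 90

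*SAP article*

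**What the plan says.** In the SAP article, the Primary outcome section explains that the CDC definition changed after the trial began and now extends to 90 days where metal implants are used. The authors respond that "we will incorporate this alternative definition of the primary outcome in a supplementary analysis", and give as the reason "to ensure the study can be utilised in future systematic reviews and meta-analyses".

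The section Analysis of primary outcome then sets two levels of checking.

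- **At 30 days.** The best/worst-case analysis ("the ITT population using an imputed dataset (best case worst case analysis") and the per-protocol analysis are run in all cases. A competing-risk analysis is added if deaths before day 30 are numerous enough, "that is if more than 5% of participants have died prior to this time point".
- **At 90 days.** The main ITT available-case analysis "will be repeated using the alternative definition of ‘deep infection’, including infections occurring up to 90 days after injury". The sensitivity analyses are conditional: "If any of the sensitivity analyses conducted for the primary endpoint (30 days) demonstrated substantially different results from the primary analysis". Only in that event does the article carry them over to the longer window, saying that "these analyses will be repeated for the rates of deep infection up to 90 days".

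The best/worst-case method is defined under Loss to follow-up, withdrawals, and missing data. In one scenario "all participants in the Standard dressing group with missing data are assumed to have a deep infection" while those missing in the NPWT group are taken as uninfected; the other scenario reverses this.

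**The concern.** The condition has three weaknesses.

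1. **It reads the wrong window.** A participant seen without infection at day 30 and then lost, withdrawn or dead before day 90 is complete for the first outcome and may be incomplete for the second. The trigger uses 30-day results only.
2. **It has no criterion.** Nothing says whether a substantial difference means a change in significance, in direction or in size. Whether the 90-day checks exist is decided once the 30-day results are known. The article's stated purpose is to limit data-driven results and selective reporting, and the competing-risk rule in the same section does carry a number.
3. **Later deaths do not count.** If no more than 5% have died before day 30, there is no 30-day competing-risk analysis to repeat, however many die between days 31 and 90.

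At stake is the reading of a supplementary estimate that the authors intend for evidence synthesis. It could be published as an available-case odds ratio with no accompanying analysis of how far missing outcomes could move it.

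**Working it through.** **Inputs.** From Sample size: 15% standard, 9% NPWT, 90% power, two-sided 5%, 615 per group, up to 20% loss, 1540 in total. From Trial status: 1548 recruited, so about 774 per arm at 1:1. Missing fractions *m* by time point are assumptions, because the plan gives none.

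**The plan's own figure.** With pooled variance under the null and a mean rate of 12%:

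n = [1.96·√(2·0.12·0.88) + 1.2816·√(0.15·0.85 + 0.09·0.91)]² / 0.06² = 614.4, so 615 per group.

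615/0.8 = 768.75, so 769 per arm and 1538 in total, against the stated 1540. The sample size reproduces.

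**How missingness moves the odds ratio.** Let k be the number missing per arm (774·m, to the nearest whole participant) and o = 774 − k the number observed. In the worst case for NPWT, infections are x_N = 0.09·o + k and x_S = 0.15·o, both out of 774 (expected counts, not rounded). Then

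OR = x_N(774 − x_S) / [(774 − x_N)·x_S], with 95% CI exp(ln OR ± 1.96·SE) and SE = √[1/x_N + 1/(774 − x_N) + 1/x_S + 1/(774 − x_S)].

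Example at 2%: k = 15, o = 759, x_N = 68.31 + 15 = 83.31, x_S = 113.85. OR = 83.31·660.15 / (690.69·113.85) = 0.70.

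Example at 5%: k = 39, o = 735, x_N = 66.15 + 39 = 105.15, x_S = 110.25. OR = 105.15·663.75 / (668.85·110.25) = 0.95.

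The imputed risk difference (NPWT minus standard) in the same scenario is (1 − m)·(−6) + 100·m percentage points.

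| Missing per arm | k | Worst-case OR (95% CI) | Risk difference, points |
|---|---|---|---|
| 0% | 0 | 0.56 (0.41–0.77) | −6.0 |
| 1% | 8 | 0.63 (0.47–0.86) | −4.9 |
| 2% | 15 | 0.70 (0.52–0.95) | −3.9 |
| 3% | 23 | 0.78 (0.58–1.05) | −2.8 |
| 5% | 39 | 0.95 (0.71–1.26) | −0.7 |
| 10% | 77 | 1.41 (1.07–1.86) | +4.6 |
| 20% | 155 | 2.74 (2.10–3.59) | +15.2 |

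Leaving k unrounded changes these odds ratios by about 0.01 at 5% and 10%.

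**Reading the table as a trigger at 30 days.** At 1–2% missing, the worst case is still significant in the same direction, so an analyst could fairly say that the result is not substantially different. At 3% significance is lost, at 5% the effect has nearly gone, and at 10% it is reversed. If there were no difference (12% in both arms), 2% missing gives 0.84 (0.62–1.13) and 1.19 (0.88–1.61). At 5% it gives 0.65 (0.49–0.88) and 1.53 (1.14–2.05), significant in opposite directions.

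**Reading it as the unchecked 90-day result.** Use the same rates at 90 days, for illustration. Going from 2% missing at day 30 to 5% at day 90 means 39 − 15 = 24 further participants per arm without an outcome; going to 10% means 77 − 15 = 62. Either is enough for the plan's own method to remove or reverse the 90-day effect, and the trigger would register neither.

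**The case against.** The case for leaving the rule alone is substantial.

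- **Best/worst-case imputation is so extreme that the trigger is easily met.** This stands. At about 3–5% missing at 30 days the conclusion changes, and at the planning figure of 20% the two scenarios give odds ratios of 0.16 and 2.74. The gap opens mainly at about 2% or less, or if the undefined term is read loosely.
- **Losses are reported anyway.** This also stands. The section on loss to follow-up reports losses by arm at each time point, with a test for differential loss, and reports deaths separately. That describes missingness but does not show its effect on the 90-day odds ratio.
- **The outcome is supplementary.** Correct. General analysis principles rests the primary conclusion on the primary analysis, and the 90-day estimate is always produced.

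A reader might also infer more than the article supports:

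- **That missingness is known to be larger at 90 days.** This is plausible with longer follow-up, but the article does not say so. The 20% in Sample size refers to primary outcome data, which is the 30-day outcome, and cannot be assigned to day 90.
- **That agreement at 30 days is uninformative.** The 90-day outcome includes every 30-day infection, in the same participants.
- **That treatment deviations build up to day 90.** The Compliance section says the dressing is applied at a single time point, so the per-protocol comparison at 30 days carries over largely intact.

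**Conclusion.** The point holds as a minor defect of specification. The 90-day checks depend on a judgement that is undefined, made after results are seen, and based on data that end at day 30. Outcomes lost or deaths occurring on days 31 to 90 cannot bring them into play.

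The consequence is conditional. With 1–2% missing at 30 days (worst-case odds ratio 0.63–0.70, still significant) and 5–10% missing at 90 days (0.95–1.41), a 90-day result that the plan's own method would overturn could be reported without that analysis. This rests on assumed missing fractions equal in both arms, the design infection rates at both time points, and unadjusted odds ratios in place of the planned mixed model. With more missing at 30 days the rule would probably work as intended. It would be wrong to read this as a threat to the trial's conclusion, which does not depend on the 90-day outcome.

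**What to change.** In Analysis of primary outcome, delete the conditional sentence. State instead that, for the 90-day definition:

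- the best/worst-case analysis will be run in all cases, using outcomes missing up to day 90;
- the per-protocol analysis will also be run in all cases; it is likely to add less, but costs little;
- the competing-risk analysis will be run if more than 5% of participants have died by day 90, which is the plan's existing criterion applied to the matching window.

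The cost is a change of wording, a re-run of existing code on a second outcome variable, and a few more supplementary results to report. Trial status places the analysis after follow-up ends, so at the time of the article this could still be settled before results were known.
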